#### Qualitative analysis

The focus groups and interviews will yield a substantial amount of complex data. To monitor progress and pursue emerging ideas, data collection and analysis will proceed concurrently [49]. The qualitative analyst will feed relevant emerging themes back to the focus group moderator and augment the interview guide as needed to capture any new ideas. Inductive analysis will be managed using N-VIVO software and will occur in three phases: coding, categorizing, and developing themes. As described earlier, all data will be coded using the TDF framework [46]. Codes will be broadly categorized corresponding to the major unit of analysis. As categories emerge, their theoretical properties will be defined. Comparisons between multiple categories will be carried out in order to locate similarities and differences between them. Finally, categories will be synthesized into themes. This process will be replicated for the qualitative data for each ‘case’.

#### Economic analysis

To address the fourth study objective, we will conduct an economic analysis [62-64] in parallel to assess costs associated with implementation versus benefits related to improvements in wait times, hospital admissions and ED revisits. To determine if the CP generates financial benefits (*i.e.*, savings), we will compare its use to standard care. We will also perform a decision analysis, from the hospital’s perspective with respect to costs, of implementation and uptake of both CP interventions. CP-associated costs will be divided into one-time start-up costs for implementation and recurrent costs for CP use and maintenance.

### Implementation costs

Throughout the project, we will track costs for all activities required for successful CP implementation at each site. This will include costs for: document customization and committee approval processes at each site, production of forms, posters and educational aides, preparation and delivery of workshops, and staff participation at these presentations. Additional costs to be tracked include refinement of web-based resources and access, travel and orientation for site champions and opinion leaders, telecommunication support, and other incidental activities. The hourly wage will be assumed to be the provincial mean for health professionals and administrators as per Ontario collective bargaining agreements, and $150 per hour for physician time.

#### Healthcare costs

Payer costs associated with emergency care for pediatric patients with asthma or V&D will be accounted for, based on ED visits, return visits, hospital admissions, and physician fees, which will be determined from the ICES administrative database. Costs for ED visits will be based on standard methodologies using resource intensity weightings (RIWs) available at ICES from the Canadian Institute for Health Information for hospital admissions and a derived RIW for ED visits. Physician fees associated with ED visits and admissions, including those for laboratory and diagnostic imaging services, will be captured through associated Ontario Health Insurance Plan billings and fee schedule. Cost data will be presented in Canadian dollars for the standard price year of 2012. To determine the effect of a full CP implementation, these health costs will also be compared for all patients at each site presenting with asthma and V&D in the pre- versus post-implementation phases.

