### Administrative data

Health administrative databases available at the Institute for Clinical Evaluative Sciences (ICES) will be used to study the impact of being on a CP on overall ED length of stay (LOS), hospital admissions, return visits within 72 hours following ED discharge for non-admitted patients, and death. Appropriate procedures will be used to link health administrative and patient specific data. The relevant databases are National Ambulatory Care Reporting System (NACRS), containing data from all Ontario EDs, and vital statistics data. Only data elements known to be reliable and valid will be used [59]. Use of NACRS data allows efficient capture of return visits, irrespective of whether the patient returns to the index hospital. These data also allow evaluation of shift-level characteristics, such as mean triage adjusted total LOS of all other patients in the ED on the same shift, which is an important contextual variable that may be associated with whether a CP was used and can be used to adjust for the LOS of the study patients. We will model whether the intervention had an impact on EDLOS, hospital admissions, return visits within 72 hours, and death; and whether ED busyness is associated with patients not being put on a pathway [66]. We will control for age, gender, Canadian Triage Acuity Scale (CTAS) rating, and EDLOS for other similar rated CTAS patients.

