### Synthesizing costs and effects

In the final economic evaluations, additional costs and outcomes will be synthesized in an incremental cost-effectiveness ratio (ICER) comparing the intervention versus control. This will result in two cost-effectiveness analyses (CEAs) relating to each CPs. The ICER for each CEA will be expressed as the incremental costs per proportion of change related to the primary clinical outcome for that CP.

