### Uncertainty analysis

In the final analysis, because an economic evaluation is always surrounded with uncertainty [64] the robustness of the ICER will be checked for sample uncertainty using non-parametric bootstrapping. The bootstrapped cost-effectiveness ratios will be subsequently plotted in a cost-effectiveness plane, in which the vertical line reflects the difference in costs and the horizontal line reflects the difference in effectiveness. The choice of treatment depends on the maximum cost, known as the ceiling ratio, that society is prepared to pay for a gain in effectiveness. Therefore, the bootstrapped ICERs will also be depicted in a cost-effectiveness acceptability curve [65] showing the probability that the intervention is cost-effective using a range of ceiling ratios.

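### Two stated analyses, the before-after cost comparison and the impact of being on a pathway, read effects from non-randomised contrasts although the by-arm contrast is available

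*Protocol article*

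**What the plan says.** **Costs.** The Healthcare costs section states a causal purpose and a method in one sentence. It opens with the purpose: "To determine the effect of a full CP implementation, these health costs will also be compared for all patients at each site". The method in full is that "these health costs will also be compared for all patients at each site presenting with asthma and V&D in the pre- versus post-implementation phases". The Economic analysis section says of savings: "To determine if the CP generates financial benefits (*i.e.*, savings), we will compare its use to standard care". The section on synthesizing costs and effects defines the ratio as "synthesized in an incremental cost-effectiveness ratio (ICER) comparing the intervention versus control", with one analysis per pathway.

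**Length of stay and related outcomes.** The Administrative data section opens by saying that the provincial databases "will be used to study the impact of being on a CP on overall ED length of stay (LOS", and adds admissions, return visits and death. Further down it says: "We will model whether the intervention had an impact on EDLOS, hospital admissions, return visits within 72 hours, and death". It also notes that how busy a shift is may be related to whether a pathway was used.

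**The general rule.** The Quantitative analysis section analyses each pathway separately. Its main effect measure, for every outcome, is the difference between arms in mean pre-to-post change, computed from hospital summaries. Table 4 lists ED length of stay, admission and 72-hour revisits as secondary clinical outcomes for both pathways.

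**The concern.** The trial randomises hospitals so that change over time and differences between patients do not have to be argued away. Two of its stated analyses give that up while still speaking of an effect.

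A before-after cost comparison at a site cannot separate the pathway from anything else that changed: fee schedules, case mix, admission practice, a bad viral season. A comparison by pathway use sets patients whom staff put on the form against patients whom they did not, and the article itself expects that choice to depend on how busy the department is.

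The fourth objective concerns costs and benefits. A report could quote a before-after saving, or a shorter stay on the pathway, as an effect of implementation when the randomised contrast shows less or nothing. The article does not say which result governs if they disagree.

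**Working it through.** **1. Timeline (Table 2, the section on outcome measures).** The phases are 9 + 9 + 12 + 7 + 5 = 42 months, which matches the stated project length. The 12-month post-implementation phase fits 3 months of settling in plus 9 months of audit (3 + 9 = 12).

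**2. Distance between the cost windows.** The outcome audits use nine-month windows, and the article says the pre period lies before the trial began. I assume that the cost comparison uses the same windows.
- If the pre window ends when implementation starts, the gap is 9 + 3 = 12 months.
- If it ends before the preparation phase, the gap is 9 + 9 + 3 = 21 months.
- Start to start, the windows are then 12 + 9 = 21 or 21 + 9 = 30 months apart. Neither is a multiple of 12. With windows ending exactly at those points, only 6 of the 9 calendar months would be shared in either case.
- A gap of 15 months (15 + 9 = 24) or 27 months (27 + 9 = 36) would match the seasons. The article gives no calendar dates, so seasonal mismatch is possible but not established. The elapsed time of at least 12 months holds either way.

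**3. What each cost contrast estimates.** For one condition, let D be the effect of implementation on mean cost and S the background change between windows.
- Before-after at implementing hospitals: D + S.
- Before-after at control hospitals: S.
- Difference in change between arms: (D + S) − S = D.

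The bias of the within-site comparison is S in full. Its sign is unknown, and neither S nor D has a figure in the article.

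**4. Price of the control.** Let hospital-level changes have variance v in each arm (assumed equal), with eight hospitals per arm. The mean change in one arm has variance v/8. The difference between arms has variance v/8 + v/8 = 2v/8. The standard error is larger by √2 = 1.41. The narrower before-after interval is centred on D + S, so its precision is no advantage.

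**5. The on-pathway contrast.** Control hospitals receive no pathway documents. Patients on a pathway should therefore appear only at hospitals allocated to it, and only after implementation. Two comparisons are possible:
- On against off pathway within those hospitals. This is not randomised, because staff decide who is put on.
- On-pathway patients against control-hospital patients. This drops the off-pathway patients from one arm only, so it is not randomised either.

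The section plans to control for age, gender, triage rating and the length of stay of other patients with similar triage ratings. That reduces confounding by measured busyness and acuity. It does not deal with unrecorded reasons for using or skipping the form. The later sentence on the intervention concerns the same four outcomes with a different exposure, and nothing says which is the effect estimate.

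**The case against.** The strongest reply is that the randomised comparison is already there. The cost-effectiveness ratio is intervention against control for each pathway. Its denominator is tied to that pathway's primary clinical outcome: "The ICER for each CEA will be expressed as the incremental costs per proportion of change related to the primary clinical outcome for that CP". The word also marks the before-after comparison as an addition. Control sites are described as continuing standard care, so comparing pathway use with standard care most naturally means the control arm. Length of stay, admission and revisits fall under the by-arm difference in change, and the intervention model covers them and death. All relevant charts are audited whether or not implementation is complete.

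All of this stands, and it limits the point. A reader might infer three stronger things that the article does not support:
- **That the randomised control is discarded for costs and length of stay.** The provisions just listed contradict this.
- **That asthma and V&D patients are pooled, so that the effect is diluted by patients whose pathway was not implemented.** The sentence names both populations but does not say they are combined, and the analysis and cost-effectiveness sections keep them apart.
- **That the bootstrap ignores hospitals.** The article says only that "the robustness of the ICER will be checked for sample uncertainty using non-parametric bootstrapping". The resampling unit is not stated, and a condensed article commonly leaves that to the full plan. The ICC is given for dichotomous outcomes only, so it cannot be used to size an error in cost.

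The reply does not remove the two sentences themselves. They state an effect purpose and name a non-randomised contrast, so this is not mere silence. Being additional does not make a before-after difference an effect.

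**Conclusion.** The point holds in a limited form. The cost-effectiveness ratio and the main outcome analyses respect the randomisation. The pre-versus-post cost comparison and the aim framed as being on a pathway do not, yet both are worded as estimates of effect.

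The cost comparison is biased by the full background change over a gap of at least 12 months, assuming the cost windows are the audit windows. The on-pathway contrast is open to confounding by busyness and other reasons for pathway use, lessened but not removed by the planned covariates. Neither bias can be quantified, because the article gives no figures for cost or length of stay. The consequence is for interpretation, chiefly under the fourth objective; the primary outcomes and the sample size are unaffected.

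**What to change.** - **Healthcare costs:** estimate the cost effect separately for asthma and V&D as the difference between allocated arms in pre-to-post change, on hospital-level data and for all eligible patients. This is the measure already defined in the Quantitative analysis section. Keep the within-site before-after figures if wanted, labelled descriptive.
- **Administrative data:** make the allocated-arm contrast the effect estimate for length of stay, admissions, return visits and death. Label any comparison by pathway use exploratory.

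**Cost:** a change of wording and no new data, since both conditions are collected at all sites in both periods. The interval for the cost effect will be wider than a one-arm before-after interval, by about 1.41 times in standard error under the equal-variance assumption above.

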### Synthesizing costs and effects

In the final economic evaluations, additional costs and outcomes will be synthesized in an incremental cost-effectiveness ratio (ICER) comparing the intervention versus control. This will result in two cost-effectiveness analyses (CEAs) relating to each CPs. The ICER for each CEA will be expressed as the incremental costs per proportion of change related to the primary clinical outcome for that CP.

### Uncertainty analysis

In the final analysis, because an economic evaluation is always surrounded with uncertainty [64] the robustness of the ICER will be checked for sample uncertainty using non-parametric bootstrapping. The bootstrapped cost-effectiveness ratios will be subsequently plotted in a cost-effectiveness plane, in which the vertical line reflects the difference in costs and the horizontal line reflects the difference in effectiveness. The choice of treatment depends on the maximum cost, known as the ceiling ratio, that society is prepared to pay for a gain in effectiveness. Therefore, the bootstrapped ICERs will also be depicted in a cost-effectiveness acceptability curve [65] showing the probability that the intervention is cost-effective using a range of ceiling ratios.

### Ethics and registration

Ethical approval has been granted for this study at the coordinating hospital (Children’s hospital of Eastern Ontario Research Ethics Board), and we are seeking site ethics approval at each hospital as their study participation is confirmed. Informed consent will be sought for interviews and focus group meetings. All research data will be stored on a secure server and will be transmitted through a secure virtual private network (VPN). It will then be securely deleted from the laptop hardrive using the software Eraser (http://www.eraser.heidi.ie). This trial is registered with ClinicalTrials.gov (http://www.clinicaltrials.gov/NCT01815710).

### Trial status

We are currently in the preparation phase, enrolling sites and seeking local ethics approvals.

## Discussion

CPs represent an important opportunity to narrow the evidence to practice gap in specific clinical settings. Given their interprofessional and typically hospital-based nature, integration of CPs into these settings involves complex interventions. Further evidence is needed, however, to guide effective methods for successful CP implementation. We have described a comprehensive study that will generate new knowledge based on a theory-based intervention strategy to implement CPs in community hospital settings. This study will address behavior change among health professionals, interprofessional team issues, patient outcomes and health economic impact. While CP outcomes are of ultimate importance, they cannot be viewed as proxies for implementation success. Through evaluation of a broad set of process and clinical outcomes, patient outcomes and clinician management—based on key interventions for each CP—can be assessed relative to degree of success in achieving implementation process measures. This knowledge can then be leveraged to inform future CP implementation activities.

We expect our study findings to be generalizable to other settings. By including EDs with varying sizes, urban/rural locations and target population patient visits, we will gain a richer understanding of relevant implementation issues across different situations. Through site visits, interviews, and continued communication throughout implementation, we also hope to identify important considerations that can be generalized to other CPs. To ensure a pragmatic approach, we have planned intervention components that can be achieved without significant additional workload or resources. Less reliance on study support and infrastructure will provide insight into success of future implementations without any such external support.

An obvious challenge for this project relates to the complex nature of the interventions being studied, and our potentially limited control in some aspects of implementation. However this affirms the importance of conducting this work in a research capacity, with a rigorous concurrent process evaluation. Another challenge relates to ED and hospital issues in particular. EDs are chaotic settings with multiple and often varying health professional team members. By focusing on pediatric conditions, which are typically an identified need in community EDs, we may uncover general issues with pediatric emergency care in these settings; many of these cannot be addressed with our intervention. Other hospital issues, such as competing priorities, budget restrictions, and staff turnover may also challenge implementation success at some of our sites. However, these are real issues confronting hospitals and must be considered for any implementation strategy.

Our research findings will be important to health professionals and organizations that are impelled to deliver evidence-based care. We will contribute to the body of evidence supporting effective strategies for CP implementation, and ultimately reducing the research to practice gaps by operationalizing best evidence care recommendations through use of CPs.

## Abbreviations

CEAs: Cost-Effectiveness Analyses; CPs: Clinical Pathways; CPGs: Clinical Practice Guidelines; cRCT: Cluster Randomized Controlled Trial; CTAS: Canadian Triage Acuity Scale; ED: Emergency Department; GEE: Generalized Estimating Equation; ICC: Intracluster Correlation Coefficient; ICD-10: International Statistical Classification of Diseases; ICER: Incremental Cost-Effectiveness Ratio; ICES: Institute for Clinical Evaluative Sciences; KI: Key Informant; LOS: Length of Stay; NACRS: National Ambulatory Care Reporting System; RIWs: Resource Intensity Weightings; TDF: Theoretical Domains Framework; V&D: Vomiting and Diarrhea; VPN: Virtual Private Network
